# Umbilical acupuncture combined with warm needle acupuncture for the treatment of residual numbness after lumbar disc herniation surgery: a protocol of a randomized controlled trial

**DOI:** 10.3389/fneur.2025.1528411

**Published:** 2025-03-11

**Keywords:** lumbar disc herniation, postoperative residual numbness, randomized controlled trial, protocol, umbilical acupuncture, warm needle acupuncture

## Abstract

**Background:**

Postoperative residual numbness following lumbar disc herniation (LDH) surgery is a relatively common symptom. Existing drugs and physical therapies are not very effective. Acupuncture is effective for the treatment of LDH, but there are limited reports on its use for postoperative numbness. Based on clinical observations and literature review, we hypothesize that combining umbilical acupuncture (UA) with warm needle acupuncture(WA) may yield superior efficacy compared to electroacupuncture(EA) alone, enhancing immune function, promoting nerve recovery, and improving microcirculation through synergistic effects, thereby filling the gap in this treatment field.

**Objective:**

This proposed trial aimed to evaluate the effectiveness and safety of UA (umbilical acupuncture) combined with WA (warm needle acupuncture) in treating residual numbness after LDH surgery. To verify the hypothesis that the combined method is superior to traditional electroacupuncture.

**Methods:**

This proposed study is a single-center, single-blind, prospective, randomized controlled trial (RCT) involving patients with LDH who were hospitalized and underwent percutaneous endoscopic lumbar discectomy (PELD) at our hospital. Patients meeting the inclusion criteria will be randomly assigned to either the treatment group (umbilical acupuncture combined with warm needle acupuncture) or the control group (electroacupuncture). The participants will be assessed on the first day after surgery, and acupuncture treatment will begin on the second day and continue for three consecutive days, with each session lasting 30 minutes. After that, the treatment mixture was changed three times a week for four weeks. All patients received standard Western medical drug treatment. After the treatment is concluded, a six-month follow-up will be conducted. The primary efficacy indicator will be the visual analog scale (VAS) score for numbness. The secondary efficacy indicators will include the 10 g monofilament test, 40 g pressure acupuncture sensation examination, Japanese Orthopedic Association (JOA) score, lower limb electromyography (H-reflex differences, F-wave conduction velocity, and latency), VAS score, traditional Chinese medicine symptom scoring, and Short Form 36-Health Survey (SF-36) score. Any adverse events occurring during the trial will be recorded. The data will be analyzed according to a predefined statistical analysis plan.

**Discussion:**

This trial combines UA with WA to create a new non-invasive treatment for numbness after LDH surgery, an area where current therapies are inadequate. If proven effective, this combination therapy could offer a safer and more effective alternative to drug treatment, and provide evidence for the integration acupuncture strategies.

**Clinical trial registration:**

http://itmctr.ccebtcm.org.cn/, identifier ITMCTR2024000328.

## Introduction

1

Patients with lumbar disc herniation (LDH) usually present with symptoms such as pain, numbness, and weakness, which negatively impact their social functioning (1, 2). Studies indicate that the incidence of residual numbness ranges from 10.0 to 40.0% (3, 4), with some studies suggesting the probability can be as high as 75% (5). Differences in surgical techniques, heterogeneity of patient populations, variations in follow-up duration, and discrepancies in study designs can all influence prevalence rates. In recent years, percutaneous endoscopic lumbar discectomy (PELD) has been standardized as a representative minimally invasive spine surgical technique for LDH (6). It offers advantages such as minimal trauma, rapid recovery, and low costs. However, in clinical practice, it is often observed that patients experience improvement in low back pain (LBP) and leg pain (LP) after surgery, they may still have residual leg numbness (RLN) or no relief (7). Persistent numbness and weakness following satisfactory pain relief are commonly seen in patients during the postoperative follow-up (8). Huang’s research found that pain recovery was fastest in the first 6 weeks after surgical decompression, while numbness recovered at a slower pace (8). Another study by Liang et al. involving 334 patients who underwent microscopic surgery for LDH, reported that after 2 years of follow-up, 112 cases of residual leg numbness (LN) were identified, yielding an incidence rate of 33.5% (7). Damage to sensory Aβfibers, which conduct sensations of vibrations and touch, may lead to a general sense of numbness (9, 10). Prolonged symptoms and severe nerve root compression may cause deformation and demyelination of nerve fibers distally, resulting in numbness and weakness (11).

Most studies have focused on the improvement of leg pain (LP) rather than numbness after lumbar decompression surgery (LDS), while the recovery of numbness has been less frequently studied (12). Currently, common treatments include neurotrophic drugs, non-steroidal anti-inflammatory drugs (NSAIDs), and medicinal block therapy; however, their long-term use may lead to undesirable adverse effects and complications (13) and insufficient evidence of effectiveness (14). There is an urgent need to identify more effective treatment options for postoperative residual numbness after LDH. Some studies have shown that acupuncture can effectively treat peripheral neuropathy (PN) caused by various conditions, improve peripheral nerve conduction velocity (NCV), and alleviate symptoms such as numbness, pain, or paresthesia in the limbs (15). Acupuncture activates A-*β*, A-*δ*, and C afferent fibers, with signals ascending through the spinal ventrolateral column to the sensory-motor cortex of the brain (16). It accelerates nerve regeneration (15). Modern medicine surveys found that LDH is treated by electroacupuncture may be through improving local microcirculation, adjusting the abnormal ultra-structure of nerve cells, regulating the immune system, decreasing the level of inflammatory cytokines, influencing the speed of nerve conduction velocity (17). In addition, acupuncture can improve the blood circulation and oxygen supply of the cauda equina, nerve root, and sciatic nerve, promote nerve recovery, and improve symptoms (18–20). Recent research suggests that acupuncture could be a potential treatment option for patients with chronic sciatica from herniated disc (21) and is strongly recommended by international guidelines for lower back pain treatment (22).

In clinical practice, we have found that umbilical acupuncture (UA) effectively mobilizes bodily functions and is characterized by fewer needles, lower pain levels, rapid results, simplicity in operation, safety, reliability, and high patient acceptance, making it a promising new treatment option. Warm needle acupuncture (WA) therapy involves placing moxa on the needle handle to transmit medicinal effects and heat through the needle to the corresponding acupoint. When the needle penetrates the skin, the warmth can transmit deep into the acupoints, effectively alleviating the symptoms of patients’ low back pain and limb numbness (23). Some modern medicine surveys found that LDH can be treated by electroacupuncture by improving local microcirculation, adjusting the abnormal ultrastructure of nerve cells, regulating the immune system, decreasing the inflammatory cytokine levels, and influencing nerve conduction velocity (17).

Therefore, further randomized controlled trials are needed to determine more effective intervention measures for this population. Based on our clinical observations, we found that the intervention group in this trial had a good effect on treating postoperative numbness, but there is a lack of high-quality research. In summary, we have designed a randomized controlled trial to evaluate the efficacy and safety of an innovative method UA (umbilical acupuncture) combined with WA (warm needle acupuncture) compared to electroacupuncture, in alleviating residual numbness after LDH surgery. This aims to provide a non-pharmacological treatment option for patients with residual numbness following LDH surgery and potentially lead to better rehabilitation outcomes for such patients.

## Methods

2

### Design

2.1

This study is a prospective, assessor-blinded, randomized controlled trial. A total of 96 participants will be recruited at the Zhejiang Provincial Hospital of Traditional Chinese Medicine. Participants will be randomly assigned to either the experimental group or the control group in a 1: 1 ratio. The trial will consist of a 4-week intervention period followed by a 6-month follow-up period. The flowchart of the research procedure is shown in Figure 1. This study will be designed and reported by the Declaration of Helsinki, the Consolidated Standards of Reporting Trials (CONSORT) (24), and the Standards for Reporting Interventions in Controlled Trials of Acupuncture (STRICTA) guidelines (25). Any potential modifications to the protocol that may affect the conduct of the study will be formally documented as amendments. Before such updates are implemented, they will be decided by the project management team and approved by the ethics committee. The trial has been registered with the Chinese Clinical Trial Registry, number ITMCTR2024000328.

**Figure 1 fig1:**
[figure not shown]
Flow chart of the study procedure.

### Recruitment

2.2

We will recruit inpatients from the Orthopedics and Acupuncture Department (patients transferred to our department for continued treatment due to residual limb numbness after PELD surgery in Orthopedics) as well as outpatients from our hospital. Eligible individuals who agree to participate in the study will sign written informed consent. We will ensure that all participants understand they have the right to withdraw from the study at any stage, and that this will not adversely affect their future treatments. The personal information of participants will be kept confidential and managed by designated professionals on our team.

### Participants

2.3

#### Inclusion criteria

2.3.1

(1) Age range from 22 to 60 years old; (2) Patients with lumbar disc herniation who underwent PELD surgery and were assessed to have residual numbness symptoms on the first day after surgery; and (3) Numbness with a VAS score greater than 40 mm (score ≥ 40 mm on a 100 mm Visual Analog Scale [VAS]).

#### Exclusion criteria

2.3.2

(1) Patients with a history of spinal surgery or severe spinal trauma; (2) Leg neurological symptoms unrelated to LDH, such as cervical spinal cord disease, neurological disorders, or lower extremity vascular diseases; (3) Patients with limb numbness caused by other reasons such as diabetes mellitus; (4) Patients with concurrent bone tuberculosis, tumors, and severe osteoporosis; (5) Patients with concurrent severe diseases affecting the cardiovascular, hematological, digestive, or other systems, or with mental illnesses; and (6) Patients with concurrent autoimmune diseases, allergic diseases, or acute/chronic infectious diseases.

#### Withdrawal and termination criteria

2.3.3

Withdrawal criteria: (1) Individuals unable to complete the entire treatment and observation process; (2) Individuals who cannot fully understand the various forms and questionnaires provided during the study and require assistance; (3) Individuals concurrently receiving other treatments; (4) Individuals with poor compliance; (5) Individuals with incomplete data affecting efficacy and safety evaluation; (6) Individuals experiencing severe adverse reactions or complications who are unsuitable for continued treatment and are therefore withdrawn from the trial; and (7) Individuals who have not completed more than 2/3 of the treatment course (including those withdrawn from the trial and lost to follow-up).

Termination criteria: Participants experiencing severe adverse events or reactions making it inappropriate to continue in the study; major errors found in the study design or significant deviations from the facts; participants who develop serious complications or deteriorate in a condition requiring emergency measures; participants withdrawing from the clinical study; patients who are uncooperative or noncompliant with treatment, despite repeated explanations from clinicians; during the trial, researchers should retain all original trial records and document in detail the reasons and timing for withdrawal. Those who have completed more than half of the treatment regimen should be included in the efficacy statistics.

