### Randomization, allocation concealment, and blinding

2.4

Eligible patients will be randomly assigned to two groups: the treatment group (receiving warm needle acupuncture combined with Western medicine) and the control group (receiving electro-acupuncture). The randomization will be performed using the CHISS software for block randomization. The size of each block is n. Once the randomization scheme is generated, it will be kept by a third party independent of this study. To ensure allocation concealment, we use sealed opaque envelopes. These envelopes are prepared by an independent member of the research team, and participants draw an envelope randomly upon enrollment in the study to determine their treatment group. Clinical researchers will obtain the specific treatment plan for each patient through designated channels (such as by phone). Assessors will not be informed of the participants’ specific group assignments throughout the follow-up period. All assessment work will be carried out by assessors independent of the treatment process. These assessors will receive rigorous training before the study begins to ensure their standardized understanding and application of the VAS score, thereby ensuring the consistency and accuracy of the assessments. Assessors will be strictly restricted from accessing participants’ treatment group information throughout the follow-up period to maintain assessor blinding. Blind statistical analysis will also be implemented during the data aggregation and analysis phase, with statisticians remaining unaware of the participants’ treatment allocations to ensure the objectivity of the statistical analysis results. In the event of serious adverse events, emergency medical situations, or requests from participants, the sealed envelope containing the blinding information will be opened by an independent third party, and the reasons, time, and personnel involved in the unblinding will be recorded in detail and reported to the relevant committee promptly. Medical decisions will be made based on the unblinding results, and participants will be allowed to withdraw from the trial if necessary.

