### Interventions

2.6

Participants in both groups of this study will be assessed on the first-day post-surgery, with treatment beginning on the second day and continuing for three consecutive days, totaling three sessions, with needles retained for 30 min each time. Subsequently, the treatments will be conducted three times a week for 4 weeks. Both treatments will be administered by trained acupuncturists who hold a valid practitioner certificate and have over 5 years of clinical experience, having undergone standardized training before the trial to ensure consistency. After discharge, patients need to undergo acupuncture treatment in the outpatient department; if numbness symptoms disappear, acupuncture treatment should be halted, and follow-up will continue per the experimental protocol.

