### Data collection and management

2.10

After participants sign the informed consent form, researchers will collect personal information such as general demographic information, clinical history, as well as baseline data including the Numbness VAS Score, 10 g Monofilament Test, 40 g Pressure Pinprick Test, JOA Score, Lower Limb Electromyography (H-reflex difference, F-wave conduction velocity, and latency), VAS Score, Traditional Chinese Medicine Syndrome Score, SF-36 (Short Form 36 Health Survey Questionnaire), etc. Outcome measures will be assessed at specified time points and recorded in the CRF. After the trial, two researchers who are not involved in data distribution or outcome assessment will independently extract data from the CRF into an Excel table. A statistician will then perform statistical analysis on this data after careful review and confirmation. To protect participant privacy, personal names will be replaced with a combination of numbers and initials. Researchers shall keep the data confidential for 5 years after the trial termination. To reduce participant dropout rates, researchers will call participants 2 days before treatment to inquire about their condition and encourage them to receive treatment as scheduled.

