### Statistical analysis

2.12

Sample size calculation was performed using PASS software (version 15.0, NCSS LLC). Based on preliminary data, the estimated mean (standard deviation) of the VAS numbness score after intervention for the treatment group (UA + WA) is 1.6 ± 1.0 cm, and for the control group (electroacupuncture) it is 2.41 ± 1.68 cm. To detect a between-group difference of 0.81 cm with 90% power (*β* = 0.10) and a two-sided *α* of 0.05, at least 41 participants are required in each group. Considering a 15% dropout rate, the final sample size is set at 48 participants per group (96 participants in total). This calculation complies with the CONSORT guidelines for randomized controlled trials.

All analyses will follow the intention-to-treat (ITT) principle, including all randomized participants. Additionally, for sensitivity analysis, a per-protocol set (PPS) analysis will be conducted, excluding participants with major protocol deviations (e.g., fewer than 8 acupuncture sessions, and use of prohibited medications). The primary outcome, the change in VAS numbness score over time points (baseline, 1 week, 4 weeks, 12 weeks, 24 weeks), will be assessed using a linear mixed-effects model (LMM). The model will include group, time, group-by-time interaction, and baseline VAS score as fixed effects. Random intercepts and slopes will account for within-individual variability. Missing data will be handled using multiple imputation (MI) with fully conditional specification (FCS) in SAS 9.4 (SAS Institute), generating 10 imputed datasets. Estimates will be combined according to Rubin’s rules. Sensitivity analysis will compare MI with the last observation carried forward (LOCF). For secondary outcomes with continuous variables (e.g., JOA, SF-36), the same LMM structure as the primary outcome will be used. For ordinal/categorical variables (e.g., TCM syndrome score), proportional odds logistic regression or generalized estimating equations (GEE) will be applied to longitudinal ordinal data. For binary outcomes (e.g., adverse events), comparisons between groups will be made using the chi-square test or Fisher’s exact test (for small sample sizes). Risk ratios (RR) and 95% confidence intervals (CI) will be reported.

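### Needing help with the study forms is a ground for withdrawal after randomisation, though it can largely be seen at baseline and no eligibility criterion screens for it

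*Protocol article*

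**What the plan says.** All references are to the protocol article.

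- **Withdrawal (2.3.3).** The second of seven withdrawal criteria reads: "Individuals who cannot fully understand the various forms and questionnaires provided during the study and require assistance".
- **Eligibility (2.3.1 and 2.3.2).** The three inclusion criteria cover age, surgery with residual numbness, and a numbness VAS threshold. The six exclusion criteria contain nothing on comprehension, literacy or completing forms. The nearest item is "Patients with concurrent severe diseases affecting the cardiovascular, hematological, digestive, or other systems, or with mental illnesses", which is a different matter.
- **Baseline data (2.10).** "After participants sign the informed consent form, researchers will collect personal information such as general demographic information, clinical history, as well as baseline data"; the list that follows includes the numbness VAS, the second VAS and the SF-36. Table 1 repeats these at later visits.
- **Timing (2.6).** Participants "will be assessed on the first-day post-surgery, with treatment beginning on the second day".
- **Allocation and blinding (2.4).** "Eligible patients will be randomly assigned to two groups", and "participants draw an envelope randomly upon enrollment in the study to determine their treatment group". Clinical researchers then learn each patient's treatment plan. Assessors, who are independent of treatment, and statisticians are kept unaware of the group.
- **Analysis (2.12).** "All analyses will follow the intention-to-treat (ITT) principle, including all randomized participants". Missing data are handled by multiple imputation.

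**The concern.** The ability to complete a questionnaire is something the patient brings to the trial. Treatment does not cause its absence, and safety does not require anyone to leave because of it. A trial that needs this ability would normally check it before allocation, when turning a patient away costs no randomised data. Here it is acted on only afterwards.

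Two things are at stake. The first is outcome data lost without need. Section 2.6 says that follow-up continues when acupuncture is halted because numbness has disappeared; section 2.3.3 makes no such provision for a withdrawn participant. Difficulty with a secondary questionnaire such as the SF-36 could therefore end collection of the primary numbness VAS as well, in someone who may be quite able to mark a 10 cm line.

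The second is discretion after allocation. Full understanding and need of assistance have no stated threshold, and nobody is named to judge them. The primary outcome is marked by the patient, so a judgement about who can manage the forms is also a judgement about who goes on supplying primary-outcome data.

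**Working it through.** The point is structural and the plan gives no figure for it, so the check is mainly a comparison of sections.

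1. **Is the trait screened for?** No. Sections 2.3.1 and 2.3.2 print full lists of criteria, and none concerns completing forms. A patient who needs help with the SF-36 but meets the printed lists is eligible.

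2. **Could it be seen before allocation?** Largely. The third inclusion criterion requires a numbness VAS score, so that scale is used before eligibility is settled. The SF-36 and the second VAS are baseline measures taken after consent, and the assessment on day 1 precedes treatment on day 2. The article does not state whether the SF-36 is completed before or after the envelope is drawn, but nothing prevents it from coming first. Because the same forms recur, most difficulty would show at baseline; some could first appear later.

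3. **What follows when the criterion is applied?** Eligible patients draw an envelope on enrolment. Anyone then found to meet the second withdrawal criterion is already allocated.

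4. **Is that person lost to the analysis?** Not under section 2.12, which retains everyone randomised and imputes. What is lost is observation. The numbness VAS is scheduled at baseline and at four later points (1, 4, 12 and 24 weeks), so a participant withdrawn before week 1 would have all four post-baseline values imputed.

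5. **Who decides?** The article does not say. Treating staff know the arm and assessors do not. Nothing in 2.3.3 or 2.4 reserves this decision to the assessors.

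6. **Scale.** With 96 participants, each percentage point meeting the criterion is 96 × 0.01 = 0.96, or about one person. The stated 15% dropout allowance is 96 × 0.15 = 14.4. The documents give no rate. Purely as an assumption, 3% would be 96 × 0.03 = 2.9 participants (2.9 / 14.4 = 20% of the allowance) and 8% would be 96 × 0.08 = 7.7 (7.7 / 14.4 = 53%). These figures illustrate scale only; no part of the conclusion rests on them.

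**The case against.** The case against has real force.

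- **Formal eligibility.** A reader might infer that ineligible patients are being randomised. The documents do not support that: under the printed criteria these patients are eligible. The narrower point, that a trait which could be screened for is not, stands.
- **Intention to treat.** A reader might also infer that they are dropped from the primary analysis. Section 2.12 says the opposite. Imputation, however, does not recover observations that an unnecessary withdrawal prevented. The sentence in 2.3.3 that includes in the efficacy statistics those past half of the regimen sits awkwardly with 2.12 and needs reconciling, but that is a separate matter.
- **Bias.** A third inference is that unblinded staff would apply the criterion unevenly. Blinded assessors carry out all assessments and are the people most likely to notice trouble with a form, and randomisation should balance a stable trait between arms. Differential withdrawal is therefore a possibility that the text leaves open, not something it shows.
- **Existing safeguards.** Written consent and the VAS entry threshold already screen in part, so the remaining gap lies mainly in the other questionnaires.
- **Prospective reading.** The criterion may be aimed at difficulty that emerges during the study. In that case assistance still serves the trial better than withdrawal.
- **Dropout allowance.** The 15% is not broken down and may already cover such cases. That lessens the effect on power but does not make the loss necessary.

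**Conclusion.** The point holds in a limited form. Section 2.3.3 provides for withdrawing randomised, eligible participants because they need help with forms, although this could largely be detected at baseline and no eligibility criterion screens for it. The consequences are avoidable missing outcome data and a subjective decision after allocation that is not reserved to blinded staff. No bias in the intention-to-treat estimate has been shown, and the size cannot be fixed because the documents give no rate.

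The conclusion assumes that withdrawal ends outcome collection, which 2.3.3 implies but does not spell out, and that difficulty with the later forms would mostly be visible when the same forms are used at baseline. It is worth correcting because the loss serves no purpose and the remedy is simple.

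**What to change.** Delete the second criterion from the withdrawal list in 2.3.3. State instead that any randomised participant who needs help with a form receives standardised assistance from the blinded assessor, and stays in follow-up and in the intention-to-treat analysis. This protects participants already enrolled as well as future ones.

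If the sponsor wants unaided completion as a requirement, add it to the eligibility criteria for future patients only, judged on the baseline VAS and SF-36 before the envelope is drawn. That step is optional: if assisted completion is acceptable, the deletion alone is enough, and an added exclusion would narrow the population.

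The cost is more than a change of wording. Section 2.14 reports that enrolment is under way, so the change must go through the amendment route in section 2.1, with ethics approval. Some questionnaires will be completed with help, which should be recorded. If the eligibility check is added, there will be a few screen failures, and patients enrolled before and after the amendment will have entered under different criteria.

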### Western medicine treatment for all included patients

2.7

All patients included in this study received basic conventional Western medicine treatment: starting from the second day after surgery, they were administered anti-inflammatory and analgesic treatment (celecoxib capsules 200 mg, 1 capsule/time, 2 times/day) combined with neurotrophic treatment (mecobalamin tablets 0.5 mg, 1 tablet/time, 3 times/day) for 28 days (Note: Patients were required to continue treatment at the outpatient clinic after discharge. If their numbness symptoms disappeared, the basic Western medicine treatment was discontinued, which was recorded in the experimental protocol, and follow-up was continued according to the experimental protocol).

Drug Sources:

Mecobalamin Tablets: Produced by Jiangxi Qingfeng Pharmaceutical Co., Ltd., Approval Number: Guoyao Zhunzi H20051440.Celecoxib Capsules: Produced by Pfizer Pharmaceutical Co., Ltd., Approval Number: Guoyao Zhunzi J20120063.

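### Withdrawal for events after randomization, and an efficacy rule based on half the regimen, do not fit an ITT analysis of all randomized participants to week 24

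*Protocol article*

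**What the plan says.** **Protocol article, section 2.3.3 (Withdrawal and termination criteria).** Criterion (3) for withdrawal reads "Individuals concurrently receiving other treatments". Criterion (4) is poor compliance. Criterion (7) covers those who have not completed more than two thirds of the treatment course, and its bracket names the withdrawn and the lost to follow-up together. Criterion (6), on severe adverse reactions, speaks of patients "who are unsuitable for continued treatment and are therefore withdrawn from the trial". Researchers are to keep the original records and "document in detail the reasons and timing for withdrawal". The section ends: "Those who have completed more than half of the treatment regimen should be included in the efficacy statistics".

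**Sections 2.6 and 2.7.** Follow-up after treatment stops is stated for one group, patients whose numbness resolves: "if numbness symptoms disappear, acupuncture treatment should be halted, and follow-up will continue per the experimental protocol". The rule for the study drugs is the same: "and follow-up was continued according to the experimental protocol".

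**Section 2.12 (Statistical analysis).** "All analyses will follow the intention-to-treat (ITT) principle, including all randomized participants". The numbness VAS is modelled at baseline and weeks 1, 4, 12 and 24. Missing values are multiply imputed, with LOCF as a sensitivity comparison. The per-protocol set is a sensitivity analysis, and its examples of exclusions are "fewer than 8 acupuncture sessions, and use of prohibited medications".

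**The concern.** Other treatment, poor compliance and a short course all happen after randomization and can be related to outcome. A patient whose leg is still numb is more likely to look for other care or to stop attending. An ITT analysis is meant to keep such patients and use their later values. Section 2.12 is written that way, since it handles this kind of deviation only in the per-protocol set. Section 2.3.3 handles the same kind of deviation by withdrawal.

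If withdrawal ends assessment, VAS values that could have been collected are lost and replaced by imputation, and the loss is related to the outcome being measured. If the closing sentence of section 2.3.3 is applied as it stands, the efficacy set is defined by treatment received and not by randomization. This is a rule of trial conduct. Section 2.14 says that enrolment is under way, and no later analysis plan can recover a visit that was not made.

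**Working it through.** **Step 1. The rules side by side.**

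| Event | Section 2.3.3 | Section 2.12 |
|---|---|---|
| Other treatment | withdrawal | prohibited medication: excluded from the per-protocol set only |
| Too few sessions | two thirds or less: withdrawal | fewer than 8: excluded from the per-protocol set only |
| Who counts for efficacy | those past half of the regimen | all randomized |

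**Step 2. Session counts.** Section 2.6 gives three daily sessions, then three a week for 4 weeks. If the first three come in addition, the total is 3 + 3 × 4 = 15.
- More than half of 15 is 8 or more. This is the exact complement of the per-protocol exclusion (fewer than 8), so the half-regimen sentence is in substance a per-protocol rule.
- Two thirds of 15 is 10, so criterion (7) catches 10 or fewer. Patients with 8 to 10 sessions are then withdrawn and yet counted for efficacy.
- A patient whose numbness resolves early, with 10 or fewer sessions, literally meets criterion (7), although section 2.6 continues that patient's follow-up.

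If the total is 12, more than half is 7 or more and criterion (7) catches 8 or fewer. The match with 8 sessions is lost, but the overlap remains (7 or 8 sessions).

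**Step 3. Possible size.** The article gives no figure on this point, so there is none to reproduce. The following is an illustration.

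*Inputs from section 2.5:* VAS 1.6 (SD 1.0) v 2.41 (SD 1.68) cm, 48 per arm.

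*Assumed:* the same means at weeks 1, 4, 12 and 24; normal values clipped to 0–10 cm; correlation between visits 0.4, 0.6 or 0.8; exit triggered by VAS of 4 cm or more; exit rate 25%, 50% or 100% of those patients. Imputation is by regression within arm on earlier post-baseline visits, with 400,000 simulated patients per arm. Baseline VAS and the full mixed model are left out.

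Standard error of the difference: √(1.0²/48 + 1.68²/48) = √(3.8224/48) = 0.28 cm. Clipping raises the true difference from 0.81 to 0.84–0.85 cm.

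Share at 4 cm or more: controls, z = (4 − 2.41)/1.68 = 0.95, about 17%; test arm, z = (4 − 1.6)/1.0 = 2.4, about 0.8%. The loss would therefore fall almost wholly on the control arm.

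Estimated difference in cm, at correlation 0.4 / 0.6 / 0.8:

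| Scenario | 25% leave | 50% leave | 100% leave |
|---|---|---|---|
| (a) Exit during follow-up on unrecorded VAS, week 24 | 0.77 / 0.79 / 0.81 | 0.67 / 0.72 / 0.78 | 0.39 / 0.49 / 0.64 |
| (b) Exit before week 4 on unrecorded VAS, week 4 | not shown | 0.65 / 0.70 / 0.75 | 0.41 / 0.47 / 0.60 |
| (b) the same, week 24 | not shown | 0.80 / 0.79 / 0.80 | 0.72 / 0.71 / 0.73 |

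(c) Exit on the recorded week-4 VAS: imputation returns 0.84–0.85, so there is no bias for the effect without other treatment. If other treatment lowers numbness by 1 cm, the treatment-policy difference is 0.80–0.81, 0.76 and 0.68–0.69 at the three exit rates. Imputation then overstates it by about 0.04, 0.08 and 0.16 cm.

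In standard errors, the largest shift with half leaving is (0.85 − 0.65)/0.28 = 0.7. With all leaving in (a) it is (0.85 − 0.39)/0.28 = 1.6 at correlation 0.4, and (0.85 − 0.64)/0.28 = 0.75 at correlation 0.8.

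**The case against.** **Condensed article.** An article need not state the period in which other treatment is barred, or that withdrawn patients stay in assessment; the full protocol may do both. This stands, and neither omission is counted as a fault here. The point rests on rules that the article does state and that do not fit together.

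**Visits may not stop.** A reader might infer that withdrawal ends assessment and that the article therefore contradicts its own ITT promise. The documents do not support that outright. No sentence says visits end, the words about leaving the trial belong to criterion (6) and not to criterion (3), and Table 1 schedules the VAS to week 24 without exceptions. Criteria (5) and (7) also partly describe patients after the event. In favour of exit are the grouping with loss to follow-up in (7) and the fact that continued follow-up is stated only for patients whose numbness resolves. Exit is plausible, not explicit.

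**The analysis already copes.** Multiple imputation keeps everyone formally in the ITT set, and section 2.12 already puts such deviations in the per-protocol set. This is why it is a poor fit and not a strict contradiction. Imputation does not restore values lost because of numbness that was never recorded.

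**Small and often conservative.** In (a) and (b) the difference shrinks, which works against a superiority claim. If *concurrently* means only alongside the 4-week course, half leaving moves the week-24 result by about 0.05 cm, or 0.2 standard errors. The overstatement in (c) arises only if a treatment-policy effect is wanted. All of this stands and limits the weight of the point.

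**The half-regimen sentence does not expressly exclude the rest.** True, but it would have no purpose if everyone randomized were counted.

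**Conclusion.** The point holds as a mismatch between stated rules. Section 2.3.3 withdraws patients for events after randomization and ties efficacy to more than half of the regimen, while section 2.12 analyses all randomized participants and treats such deviations as per-protocol matters. That withdrawal costs VAS data depends on the plausible but unstated reading that assessment ends there.

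The size and direction of any bias cannot be derived from the documents. Under the assumed mechanisms the estimate may shrink, stay put or overstate the treatment-policy effect. It moves by more than one standard error only if every patient at 4 cm or more leaves, and not even then at correlation 0.8. The effect is probably modest. A reader might infer that the ITT analysis is invalid or the primary result seriously biased, and neither follows. It is a cheap improvement that should be made, with medium confidence.

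**What to change.** Amend section 2.3.3 as follows:
- Meeting a withdrawal criterion stops study treatment at most. All Table 1 visits continue to week 24 unless the patient withdraws consent.
- The date and type of any other treatment are recorded.
- Values observed after that point are used in the ITT model. Other treatment and short courses are handled only in the per-protocol set.
- The half-regimen sentence is deleted, or confined to the per-protocol set and worded to agree with the rule of fewer than 8 sessions.

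Whether other treatment should be permitted is a clinical matter and is left open.

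Cost: one protocol amendment and one CRF field, next to the reasons and timing of withdrawal that are already recorded. No extra patients and no visits beyond Table 1 are needed. Downside: the ITT contrast then describes the assigned strategy together with the effect of any other treatment patients take.
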